#### Recording and reporting of adverse events

2.8.2

Any AE was recorded in the CRF by the investigator within 24 h. AEs, SAEs, and unanticipated events will be recorded following reporting standards and reported to the Ethics Committee and other regulatory authorities. The principal investigator will regularly review all adverse events, and the Ethics Committee will also receive interim results. If necessary, meetings will be held to reassess the benefits and risks of the trial.

#### Security analysis

2.8.3

AEs are classified and reported according to common AE evaluation criteria.

Incidence = (number of patients with AE/total number of patients) × 100%

Fisher’s exact test is used to compare intergroup incidence.

Individual list description risk ratio (RR), and confidence interval (CI) calculations are performed for SAEs. Comprehensive recording and analysis ensure subject safety and data integrity, in order to complete statistical analysis and help investigators understand the potential effects of acupuncture.

### Data collection and management

2.9

The experimental protocol was monitored and revised by acupuncturists, physicians, researchers, and statisticians. Additionally, quality control measures such as informed consent, subject screening, intervention, statistical analysis, and data management are reviewed. In addition, there is regular supervision by clinical experts. This study uses the Case Report Form (CRF) to collect data. Manuscript information and a web database of all study results will be recorded, and information in the repository will be made available after the study is completed.

### Data processing and statistical analysis

2.10

Data analysis was performed by qualified personnel not involved in the study using the Modified Intention-to-treat (mITT) principle. mITT was defined as participants who were randomized, received at least one treatment, and were statistically analyzed using the SPSS (IBM SPSS Statistics, Version 26.0) software. The significance level was set at 5%. Continuous variables that conform to the normal distribution are represented by mean ± standard deviation (x ± s), and non-normal continuous variables are represented by median and quartile [M (P25, P75)]. Categorical variables are expressed as frequency (percentage) using a chi-square or Fisher precision test. For primary and secondary outcomes, an independent sample T-test was used to compare groups if normal distribution and homogeneity of variance were met; otherwise, the Mann–Whitney *U* test was used. Intragroup comparisons were performed using the paired sample T-test. According to missing outcome data, the last observation carried forward (LOCF) method or multiple interpolation was used to fill in the missing values. In addition, sensitivity analyses were performed to clarify the robustness of the results by comparing the conforming protocol analysis set (PPS) analysis with the ITT analysis set. The data obtained by sEMG were analyzed with the main outcome, FMA-UE, using Person/Spearman correlation analysis. Finally, we calculated the BI index to evaluate the success of blinded implementation.

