#### Withdrawal criteria

2.2.3

(1) Withdrawal as decided by the investigator:

① During the study, the participant has certain comorbidities, complications, or pathological changes that make it unsuitable to continue the study.② In the study, the participant has poor compliance, which may affect the evaluation of effectiveness and safety.③ The participant breaks the blindness or exposes the blinded data in an emergency.④ Adverse events and serious adverse events occurred, making a participant unsuitable to continue to receive the study.

(2) Withdrawal from the study.

According to the provisions of the informed consent, participants have the right to withdraw from the study midway, or the participants may not explicitly withdraw from the study, but may no longer receive medication and testing, and lose follow-up (which is also classified as a “withdrawal,” called “drop”). The reasons for withdrawal, such as poor efficacy, intolerance to certain adverse effects, inability to continue the clinical study, economic factors, and failure to explain the reasons for the loss of visits, should be understood as much as possible and recorded.

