### Randomization and allocation concealment

2.3

In this study, a centralized randomization system developed by the research team randomly assigned patients to the acupuncture and sham acupuncture groups in a 1:1 ratio. The module size was set to 4, and 37 patients were randomly assigned to each group. All assignment information was unpredictable and invisible until participant inclusion, and the assignment sequences were directly notified to the acupuncturist by the system to ensure fairness of the assignment sequence hiding and randomization process. After the investigator confirms the qualified cases, a third party submits the application to the central randomization system, which automatically assigns the group information according to the randomization method and sends the group information to the investigator and acupuncturist.

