### Blinding

2.4

The primary researchers are unaware of the patients’ group assignments. The efficacy evaluation is conducted by third-party personnel, and the database for data statistics is set up with a first-level blind, so the statisticians do not know the specific group details. Due to the limitations of acupuncture procedures, acupuncturists cannot be blinded. They are aware of the patients’ group assignments. All operations are trained in accordance with established Standard Operating Procedures (SOP). The acupuncture blinding auxiliary device was independently developed by the team and has been proven to effectively maintain blinding. According to the requirements, Type A and B blind acupuncture aids will be used in the MA and SA groups, respectively. Auxiliary device for acupuncture blind is presented in Figure 2.

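### The primary analysis set omits randomised patients who never start treatment, and knowledge of the arm before the first session could influence who starts

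*Protocol article*

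**What the plan says.** Section 2.10 states that the data are analysed "using the Modified Intention-to-treat (mITT) principle" and defines the set: "mITT was defined as participants who were randomized, received at least one treatment". No other set is assigned to the primary FMA-UE comparison. Missing outcomes are handled in the same section: "the last observation carried forward (LOCF) method or multiple interpolation was used to fill in the missing values". The sensitivity analysis is described as "comparing the conforming protocol analysis set (PPS) analysis with the ITT analysis set", but the section does not define an ITT set distinct from the modified one.

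On who knows the arm, section 2.3 says "the assignment sequences were directly notified to the acupuncturist by the system", and later that the system "sends the group information to the investigator and acupuncturist". Section 2.4 adds: "Due to the limitations of acupuncture procedures, acupuncturists cannot be blinded". Section 2.2.3 lists grounds for "Withdrawal as decided by the investigator".

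**The concern.** Leaving out patients who never start is usually harmless when nobody who could affect starting knows the arm, because the omitted patients should then be alike in the two groups. That condition is not secured here. The acupuncturist who delivers the first session has the allocation beforehand. On the wording of section 2.3 so does the investigator, to whom section 2.2.3 gives withdrawal decisions. The procedures also differ physically: sections 2.6.1 and 2.6.2 describe penetrating needles in one arm and a blunt, non-penetrating needle in the other.

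If patients with a poorer outlook failed to start more often in one arm, the primary comparison would no longer be between the groups as randomised. With 37 patients per arm, a handful of such losses could move the FMA-UE difference by a noticeable part of the margin.

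**Working it through.** **Inputs.** From section 2.5: mean difference 11.5, SD 10.4, superiority margin 4.6, α = 0.05, power 0.80, dropout 20%, 37 per arm. The article does not give the number of non-starters (k) or how far their mean FMA-UE lies below that of the patients kept (D). Both are assumptions below.

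**Step 1: the plan's own figure.** The distance from the margin is 11.5 − 4.6 = 6.9. With one-sided α = 0.05:

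n per arm = 2 × (1.645 + 0.842)² × 10.4² / 6.9² ≈ 28.1, so 29, or 58 in total.

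A noncentral-t check also gives 29 per arm (power 0.803). Allowing for dropout, 29 / 0.8 = 36.25, so 37 per arm and 74 in total. The stated 58 and 74 are reproduced. A two-sided 5% test gives 72 by the same formula and does not match, so the one-sided form is used below.

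**Step 2: does anything in section 2.10 bring non-starters back?** Imputation fills gaps for members of the analysed set, and a patient without a session is not a member. The ITT set in the sensitivity analysis is undefined and may be only another name for the modified set. Neither repairs the primary comparison.

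**Step 3: size of the shift.** If k of 37 patients in one arm are omitted and their mean is D below the mean of those kept, the full-arm mean is the kept mean minus kD/37. Omitting them therefore raises that arm's mean by

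b = (k / 37) × D.

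**Step 4: error at the margin.** Suppose the true difference is exactly 4.6 and the test is one-sided at 5%. Then approximately

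error = P(Z > 1.645 − b / SE), with SE = 10.4 × √(1/37 + 1/(37 − k)).

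For k = 1 and D = 10.4: b = 0.28, SE = 2.43, b/SE = 0.115, error = P(Z > 1.53) ≈ 6.3%.

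Losses in the acupuncture arm only, D = 10.4 (1 SD); errors simulated with 50,000 trials per row:

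| k | shift b | share of 4.6 margin | error at margin |
|---|---|---|---|
| 0 | 0 | 0% | about 5% |
| 1 | 0.28 | 6% | 6.3% |
| 2 | 0.56 | 12% | 7.9% |
| 3 | 0.84 | 18% | 9.7% |

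**Step 5: range.**
- Non-starting unrelated to arm or to prognosis: shift 0.
- D = 5 points: shifts of 0.14, 0.27 and 0.41 for k = 1, 2, 3.
- Upper bound, with the k lowest scorers on the final outcome removed from the acupuncture arm: simulated shifts of 0.63, 1.13 and 1.62, with errors of about 9%, 13% and 18%.

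If the losses fell in the sham arm instead, the shift would have the opposite sign.

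**The case against.** The strongest reply is that the article gives no sign that this will happen, and much of that stands.

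- A reader might infer that the acupuncturist controls who is left out. No section gives the acupuncturist power to refuse or exclude a patient. Eligibility is confirmed before randomisation (2.3), withdrawal belongs to the investigator or the participant (2.2.3), and delivery follows a standard procedure (2.4, 2.6). This protection is weakened because section 2.3 also sends the allocation to the investigator, which conflicts with the statement in 2.4 that the primary researchers are unaware of it.
- One session out of 20 is enough to enter the set, so a late start removes nobody. Participants are inpatients whose treatment is masked by a device, so few may receive no session at all. Device masking does not, however, address decisions by staff who know the arm.
- A reader might infer that the losses would be invisible. They would not: section 2.1 commits to CONSORT 2025 reporting and the Figure 1 caption to a flow chart by group, so the gap between randomised and analysed numbers would show. Seeing the gap does not correct the estimate.
- A reader might take the 0.6 to 1.6 point shifts as the likely size. They require removing, in one arm only, the worst scorers on an outcome nobody can observe before the first session. They are a ceiling.
- The unseen analysis plan may define an all-randomised set. Even so, the article fixes the treated set as the basis of the analysis.
- Including non-starters is not free of assumptions. Those without later scores must be imputed, and carrying a baseline value forward assumes no recovery.

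**Conclusion.** The point holds as a conditional weakness in the choice of primary set. Membership depends on an event after randomisation, at least one unmasked member of staff knows the arm before it, and section 2.10 contains no safeguard. The documents support saying that exclusions could depend on the arm, not that they will.

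The size is unknown. It is zero if non-starting is unrelated to arm or prognosis, and about 0.3 to 0.8 FMA-UE points in the 1 SD illustration, with error at the margin of about 6% to 10%. These figures assume 1 to 3 losses confined to the acupuncture arm, SD 10.4, and a one-sided 5% test against 4.6. The sample size implies that test; section 2.10 itself states only a 5% level and mentions no margin. The change is worth making because it is cheap, even though the likely effect is modest.

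**What to change.** In section 2.10:

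1. Define the primary set as all randomised patients, analysed in the arm assigned.
2. Seek the scheduled outcome assessments from patients who never start. Where none can be obtained, use multiple imputation that includes baseline FMA-UE, which Table 1 schedules at allocation, rather than LOCF.
3. Keep the set treated at least once as a sensitivity analysis, and state what the ITT set named there contains.
4. Give the number of non-starters and their reasons by arm in the planned flow chart.

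Sections 2.3 and 2.4 should also be reconciled on whether the investigator receives the allocation.

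The cost is a few sentences and some effort to assess patients who do not start. The estimate may be slightly diluted by untreated patients, and any without later scores bring an imputation assumption that cannot be tested. The planned total stays at 74, since the 20% allowance already covers missing outcomes.

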#### Inclusion criteria

2.2.1

The Diagnostic Points of Various Major cerebrovascular diseases in China in 2019 were formulated as per the Branch of Neurology of the Chinese Medical Association (18). The following patients will be included:

(1) They meet the above diagnostic criteria for ischemic stroke.(2) Aged between 35 and 80 years, sex is not limited.(3) 2 weeks to 6 months have passed following the first stroke.(4) Objectively measured upper limb dysfunction; National Institutes of Health Stroke Scale (NIHSS) score ≥ 5.(5) Conscious and stable vital signs.(6) Provide signed informed consent.

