### Sample size

2.5

The sample size calculation for this study was based on the primary outcome measure, the FMA-UE score. According to preliminary pilot results, the mean difference (MD) in FMA-UE scores between the acupuncture and control group after treatment was 11.5, with a standard deviation (SD) of 10.4. Meanwhile, the minimal clinically important difference (MCID) for the Chinese version of the FMA-UE is 4.6. This study was a superiority design, using PASS 15.0 software for sample size estimation. An independent samples t-test was employed, with a significance level set at *α* = 0.05 and power *β* = 0.8. It is estimated that the acupuncture group must reach the MCID value compared to the sham acupuncture group to be clinically meaningful. Therefore, the superiority margin is set equal to the MCID value of 4.6. The minimum sample size calculated is 58 cases. Considering a 20% dropout rate, the final sample size was determined to be 74 cases (37 cases each in the MA and SA groups).

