### Outcomes

2.7

At baseline, 2 and 4 weeks post-treatment, and at the 3-month follow-up, several experienced and trained third-party personnel are blinded to the outcome indicators. Simultaneously, sEMG data are collected by a specialized, trained rehabilitation therapist who is not involved in the design, and the RMS, iEMG, and MF of the affected upper limb core muscle group are compared before and after treatment.

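### The primary FMA-UE comparison ignores the baseline score that every patient provides; naming ANCOVA would add precision for about one degree of freedom

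*Protocol article*

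**What the plan says.** Section 2.10 (Data processing and statistical analysis) fixes the test: "For primary and secondary outcomes, an independent sample T-test was used to compare groups". That choice is conditional on the data looking normal with equal variances. When the check fails, the plan falls back on a rank test, which is also unadjusted: "otherwise, the Mann–Whitney *U* test was used". Section 2.5 (Sample size) plans on the same basis: "The sample size calculation for this study was based on the primary outcome measure, the FMA-UE score", and "An independent samples t-test was employed". No covariate, ANCOVA or mixed model is mentioned anywhere in the article.

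The baseline value is available. Section 2.7 (Outcomes) sets the assessments "At baseline, 2 and 4 weeks post-treatment, and at the 3-month follow-up", and Table 1 marks FMA and each secondary scale at baseline, week 2, week 4 and 3 months.

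Section 2.3 describes 1:1 allocation in blocks of 4 with 37 per group and states no stratification by baseline severity. The entry window in 2.2.1 is "2 weeks to 6 months have passed following the first stroke".

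The article does not say whether the test is applied to the post-treatment score or to the change from baseline. Section 2.5 speaks of a difference after treatment; the MCID sentence in 2.7.1 speaks of change.

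**The concern.** A baseline measurement of the same scale usually predicts the later score. A two-sample test on the final score leaves the variation that baseline explains in the error term, so the confidence interval is wider than the collected data allow. Any chance difference between the arms at baseline also stays in the estimate. With 37 per arm, no stated stratification by severity and patients entering at quite different stages of recovery, such a difference need not be small relative to the 4.6-point margin against which the trial was sized. The Mann–Whitney fallback has the same limitation.

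**Working it through.** **Inputs from section 2.5.** Mean difference 11.5; SD 10.4 (of score or of change, not stated); superiority margin 4.6; α = 0.05 (sidedness not stated); power 0.80; minimum 58; dropout 20%; final 74.

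**Assumption.** The correlation r between baseline and post-treatment FMA-UE is not in the document, so a range is shown.

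**Step 1: reproduce the planned size.** The distance from the margin is 11.5 − 4.6 = 6.9. With n = 29 per arm the SE is 10.4 × √(2/29) = 2.73, and the noncentrality is 6.9 / 2.73 = 2.53. At one-sided 5% with 56 df the critical value is 1.673 and noncentral-t power is 80.3%. With 28 per arm it is 79.0%. So 29 per arm, 58 in total, reproduces. Allowing for dropout, 29 / 0.8 = 36.25, rounded up to 37 per arm, gives 74. Two-sided 5% would need 37 per arm before dropout, so only the one-sided variant gives 58.

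**Step 2: ANCOVA if 10.4 is the SD of post-treatment scores.** Residual SD = 10.4 × √(1 − r²). Same 29 per arm, margin 4.6 and one-sided 5%, with one df lost (55 df):

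| r | Residual SD | Power |
|---|---|---|
| none (t-test) | 10.40 | 80% |
| 0.3 | 9.92 | 83% |
| 0.5 | 9.01 | 89% |
| 0.7 | 7.43 | 97% |

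**Step 3: ANCOVA if 10.4 is the SD of change and the t-test is run on change.** With equal SDs σ at both visits, the change variance is 2σ²(1 − r) and the ANCOVA residual variance is σ²(1 − r²). Their ratio is (1 + r)/2, so residual SD = 10.4 × √((1 + r)/2):

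| r | Residual SD | Power |
|---|---|---|
| none (t-test on change) | 10.40 | 80% |
| 0.3 | 8.38 | 93% |
| 0.5 | 9.01 | 89% |
| 0.7 | 9.59 | 86% |
| 0.9 | 10.14 | 82% |

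The gain runs the other way here: the higher the correlation, the closer the change score already is to ANCOVA.

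**Step 4: the cost.** At r = 0, where adjustment brings nothing, power goes from 80.26% to 80.24%.

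**Step 5: chance baseline imbalance.** Assuming the baseline SD is also about 10.4, the SE of the baseline difference with 37 per arm is 10.4 × √(2/37) = 2.42 points. About one trial in three would start more than 2.4 points apart, and the 95% range is ± 1.96 × 2.42 = ± 4.7 points, about the size of the margin.

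**The case against.** The strongest reply is that nothing here is an error. Under randomization the two-sample t-test is unbiased, its standard error already allows for chance baseline imbalance, and the sample size was computed for that same test. This stands, and it limits the point to efficiency. A reader might infer bias or an inflated type I error; the documents do not support either.

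A reader might also infer that the unadjusted test leaves the trial underpowered. Figures of that kind can be produced: at 29 per arm, power is about 70% for a two-sided 5% test against 4.6, and about 74% for a one-sided test against the 5.2 MCID in 2.7.1. Those shortfalls come from the unstated sidedness and from the two MCID values, which are separate matters. Under the inputs that give 58, the unadjusted test meets its 80% target and ANCOVA adds to it.

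The size of the gain also rests on an unknown correlation. At r = 0.3 with 10.4 as the score SD it is only about 3 percentage points. If change is analysed, baseline is already used in part, the gain at r = 0.9 is about 2 points, and the imbalance argument weakens. This too stands; hence the ranges.

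Two further inferences should be avoided. Entry is not open to any arm severity: 2.2.1 requires measured upper limb dysfunction and an NIHSS of at least 5, and 2.2.2 excludes severe spasticity. And 2.10 lists paired within-group tests but does not call them evidence of efficacy.

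Finally, section 2.1 says an analysis plan is available with the registration and it might name covariates. That does not dispose of the point, because 2.10 itself specifies the primary test.

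**Conclusion.** The point holds as a recommended improvement. Section 2.10 fixes an unadjusted primary test although the baseline value is collected on every patient. The consequence is lost precision and less protection against chance imbalance; the validity of the test is not in question. Against 80% for the planned test, ANCOVA at the same size gives about 83% to 97% for r from 0.3 to 0.7 if 10.4 is the score SD, or about 93% down to 82% for r from 0.3 to 0.9 if 10.4 is the SD of change. These figures assume one-sided 5%, margin 4.6, 29 per arm and the stated correlations; the change-score figures also assume equal SDs at both visits. The 2.4-point SE for baseline imbalance assumes a baseline SD near 10.4. ANCOVA corrects the linear effect of the covariates in the model; it does not remove imbalance in other factors.

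**What to change.** In 2.10, name one primary analysis: ANCOVA of week-4 FMA-UE on group and baseline FMA-UE, optionally with time since stroke, which has to be established anyway to apply the inclusion window. Report the adjusted mean difference with its confidence interval and judge it against the margin. Once baseline is a covariate, modelling the final score or the change gives the same treatment estimate, so the question of which one is tested also falls away.

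Use the same model for each secondary scale with that scale's own baseline. Keep the unadjusted t-test, or the Mann–Whitney test where its condition applies, as a sensitivity analysis, so that the primary method no longer depends on a check of the data.

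The cost is a change of wording before unblinding and one or two degrees of freedom. No new data and no change in sample size are needed.

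### The data choose the primary FMA-UE test: unequal variance or non-normality moves it from the mean difference that sized the trial to a rank test that does not address that difference

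*Protocol article*

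**What the plan says.** Section 2.10 (Data processing and statistical analysis) gives one rule, which covers the secondary scales as well as FMA-UE: "an independent sample T-test was used to compare groups if normal distribution and homogeneity of variance were met; otherwise, the Mann–Whitney *U* test was used". Both conditions must hold for the t-test to be used. If either fails, the rank test replaces it, and no t-test for unequal variances is named.

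Section 2.5 (Sample size) puts the primary question in means. The pilot input is that "the mean difference (MD) in FMA-UE scores between the acupuncture and control group after treatment was 11.5, with a standard deviation (SD) of 10.4". For the test it states: "An independent samples t-test was employed". The superiority margin is set at 4.6 FMA-UE points, the minimum is 58 patients, and 20% dropout brings this to 74 (37 per arm). One SD is given. There are no arm-specific SDs and nothing on the shape of the distribution.

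**The concern.** The hypothesis behind the primary p-value is settled only after the outcome data are seen. The reference distribution of Mann–Whitney U assumes the same distribution in both arms. It speaks to a mean difference, or to a 4.6-point mean margin, only if the arms differ by a pure shift in location. Unequal variance contradicts that condition, so the rule selects the rank test in a case where it cannot answer the question in section 2.5. The usual remedy for unequal variance, Welch's t-test, keeps that question.

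Treatment can itself trigger the switch. If only some patients respond, the acupuncture arm becomes wider and skewed. A mean benefit carried by a minority could then be missed, or arms with equal means but different shapes could be declared different.

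**Working it through.** **1. The plan's own figure.** Inputs from section 2.5: difference 11.5, SD 10.4, margin 4.6, α 0.05, power 0.80. The effective difference is 11.5 − 4.6 = 6.9. Per arm, one-sided:

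n = 2(1.645 + 0.842)² × 10.4² / 6.9² = 28.1, rounded up to 29, so 58 in total.

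Then 29 / 0.8 = 36.25, rounded up to 37 per arm, or 74. The exact t calculation also gives 29 (power 0.803). A two-sided test would need 72 (74 by exact t), so the plan's figure is a one-sided t-test of means against a margin.

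**2. How often unequal variance triggers the switch.** Simulated normal data, 29 and 37 per arm, average variance held at 10.4², larger SD in the acupuncture arm. The SD ratios are assumptions. Levene's test is significant in about 50–60% of trials at ratio 1.5, 90–96% at ratio 2 and about 100% at ratio 3.

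**3. Normal arms, unequal SDs.**
- Power at a true difference of 11.5 against 4.6, one-sided 5%: Welch 80% at 29 per arm and 88–89% at 37; Mann–Whitney 77–79% and 85–87%. The loss is about 2 to 4 points.
- Rejection with equal means, two-sided 5%: Mann–Whitney 5.6–5.9% at ratio 2 and 6.5–7.1% at ratio 3; Welch 4.6–5.4%.

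**4. Skewed arms, same margin test, 29 per arm (shapes assumed).**
- Right skew, SD ratio 3, Welch against Mann–Whitney: gamma with shape 4, 83.1% and 61.1%; lognormal, 85.7% and 63.0%; gamma with shape 1, 86.3% and 53.2%. Losses are 22 to 33 points.
- Right skew, ratio 2: losses of 5 to 14 points. At ratio 1.5 with gamma shape 1 the rank test gains (83.6% to 91.4%).
- Left skew, ratio 3: the rank test gains, for example 77.3% to 89.5% and 76.7% to 96.7%.
- Equal means, ratios 1.5 to 3: Mann–Whitney rejects in 6.5–41%, Welch in 4.8–7.3%.

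**5. Responder patterns.** 37 per arm, 3000 runs, scores rounded and clipped to 0–66, two-sided 5% against zero difference. A fraction of the acupuncture arm gains a fixed amount and the rest gain nothing. The planned rule is coded as Mann–Whitney if Levene's test or Shapiro–Wilk in either arm gives p < 0.05, otherwise Student's t. The modified rule uses Welch when only the variance check fails and keeps Mann–Whitney for non-normality. Simulation error is at most about √(0.5 × 0.5 / 3000) = 0.9 points.

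| Pattern | Welch | Planned rule | Modified rule |
|---|---|---|---|
| 25% gain 28, SD 8 | 73% | 44% | 49% |
| 25% gain 24, SD 6 | 79% | 47% | 49% |
| 30% gain 24, SD 8 | 79% | 59% | 67% |
| 25% gain 24, SD 10.4 | 52% | 42% | – |
| 40% gain 28.75, SD 10.4 | 93% | 82% | – |
| 50% gain 23, SD 10.4 | 96% | 93% | – |
| 50% gain 14, SD 10.4 | 75% | 74% | – |
| All gain 11.5, SD 10.4 | 99.6% | 99.6% | – |

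In the first three rows the planned rule loses 29, 32 and 20 points. Mending only the variance clause recovers 49 − 44 = 5, 49 − 47 = 2 and 67 − 59 = 8 of them.

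With sham shifted so that the means are equal, the planned rule rejects in 14.6% (25% gain 28, SD 8) and 20.9% (25% gain 24, SD 6). The modified rule gives 14.6% and 20.7%, and Welch about 5%. At SD 10.4 with 25% gaining 24, the planned rule rejects in 6.0%.

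**The case against.** The strongest reply concerns size and cause. A reader might infer that the rule costs 20 to 30 points of power whenever variances differ. The documents do not support that. Losses of that size need a quarter to 30% of patients gaining 24–28 points with everyone else gaining nothing and an SD of 6 or 8, or right skew with an SD ratio near 3. None of this is in the article. At its own SD of 10.4 the responder patterns lose between 0 and about 12 points.

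A reader might also infer that unequal variance alone does the harm. In the SD 6–8 patterns most of the power loss, and essentially all the excess rejection, comes from the switch for non-normality. That split was made only for those patterns and need not carry over to SD 10.4.

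Three further replies have weight. Rank tests for non-normal data are common practice. The equal-means cases are contrived: three quarters of the acupuncture arm sit 6 to 7 points below sham, so the distributions do differ and rejection is false only under the mean null. And the responder powers refer to a two-sided test of zero difference, not to the planned margin test.

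These replies limit the magnitude. They do not touch the mismatch: section 2.5 asks about mean points against 4.6, and under section 2.10 the data decide whether that question is tested.

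**Conclusion.** The concern holds as a moderate defect in the choice of analysis. Section 2.10 lets the data pick the primary hypothesis, and for unequal variance it picks a test that does not remedy the problem and does not test the quantity that sized the trial.

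The practical cost cannot be fixed from the documents. It is small for normal arms with unequal spread, nil under a uniform shift, and material only if unequal spread comes with unequal shape. It can also run in favour of the rank test. The larger figures rest on assumed response patterns and should be quoted only with those assumptions. The case for the change does not depend on them.

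**What to change.** In section 2.10, replace the conditional rule for FMA-UE with one named primary analysis of the mean difference that allows unequal variances. This can be Welch's t-test with a confidence interval in scale points, read against the 4.6 margin, or a regression model with heteroscedasticity-robust standard errors. State that no normality or variance test selects the primary analysis. Keep Mann–Whitney U as a labelled sensitivity analysis. The same sentence can serve the secondary scales.

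The change is one sentence and needs no extra data. Its price is a negligible loss of degrees of freedom when variances are equal, and possibly lower power than a rank test in some skewed patterns, such as the left-skewed cases above.

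### LOCF should not be an option for the primary FMA-UE analysis: it freezes dropouts at a baseline or week-2 score while patients may still be recovering

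*Protocol article*

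**What the plan says.** Under Data processing and statistical analysis (2.10), the article states for missing outcomes that "the last observation carried forward (LOCF) method or multiple interpolation was used to fill in the missing values". Multiple interpolation is evidently multiple imputation. The main analysis set is mITT: randomised patients who had at least one treatment. On robustness, the section says that "sensitivity analyses were performed to clarify the robustness of the results by comparing the conforming protocol analysis set (PPS"; the comparator is the ITT set.

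Four other places bear on this:

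- Inclusion criteria (2.2.1): entry when "2 weeks to 6 months have passed following the first stroke".
- Outcomes (2.7): scoring takes place "At baseline, 2 and 4 weeks post-treatment, and at the 3-month follow-up". Table 1 shows FMA-UE at baseline, week 2, week 4 and 3 months.
- Sample size (2.5): "Considering a 20% dropout rate, the final sample size was determined to be 74 cases".
- Withdrawal criteria (2.2.3): "The reasons for withdrawal, such as poor efficacy, intolerance to certain adverse effects, inability to continue the clinical study" are foreseen, so leaving may be related to outcome or to arm.

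**The concern.** LOCF assumes that a patient who leaves stops changing at the last visit. That sits badly with a trial that measures motor recovery in patients as early as 2 weeks after stroke. A patient who has one session and leaves in week 1 stays in the mITT set, and under LOCF enters the week-4 and 3-month comparisons with the baseline score. One who leaves after week 2 enters with the week-2 score.

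Two things are at stake. If acupuncture works, frozen scores pull the estimated difference towards zero, and the planned power goes with it. If dropout differs between arms, the arm that loses more patients is penalised, whether or not there is an effect. Recruiting 74 rather than 58 replaces lost numbers but does not remove this bias. Comparing PPS with ITT does not expose it either, because it changes who is analysed and not what is assumed about the missing scores.

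**Working it through.** **Inputs from section 2.5.** The difference "between the acupuncture and control group after treatment was 11.5, with a standard deviation (SD) of 10.4"; margin 4.6; alpha 0.05; power 0.8; 20% dropout; 37 per arm.

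**Assumptions, not in the document.** The share f of the week-4 gain present at the last visit (0 if only baseline was seen, 0.5 if week 2 was seen); mean recovery in the sham arm; dropout by arm. The SD is held at 10.4, and f is the same in both arms.

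**1. The plan's own figure.** The effect beyond the margin is 11.5 − 4.6 = 6.9. A one-sided 5% test with SD 10.4 and power 0.8 needs 29 per arm, or 58 (exact t power 0.803). Then 29 / 0.8 = 36.25, rounded up to 37 per arm, or 74. Both stated figures reproduce with a one-sided alpha; a two-sided alpha does not give 58.

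**2. Formula.** For an arm with true mean gain g and dropout d, the expected gain under LOCF is g × [(1 − d) + d × f].

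**3. Equal 20% dropout.** The factor is common to both arms, so sham recovery cancels.

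- f = 0: 11.5 × 0.8 = 9.2, a bias of −2.3.
- f = 0.5: 11.5 × 0.9 = 10.35, a bias of −1.15.

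**4. Power against the 4.6 margin, one-sided 5%, t-test.** With 37 per arm, SE = 10.4 × √(2/37) = 2.418.

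| Case | Patients per arm | Difference | (Difference − 4.6) / SE | Power |
|---|---|---|---|---|
| Unbiased, completers | 29 | 11.5 | 6.9 / 2.731 = 2.53 | 0.80 |
| Unbiased, completers | 30 | 11.5 | 6.9 / 2.685 = 2.57 | 0.81 |
| LOCF, f = 0.5 | 37 | 10.35 | 5.75 / 2.418 = 2.38 | 0.76 |
| LOCF, f = 0 | 37 | 9.2 | 4.6 / 2.418 = 1.90 | 0.59 |

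The completer rows are the fair comparator, since 37 × 0.8 = 29.6 patients per arm would be observed.

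**5. Unequal dropout with a true 11.5-point effect** (sham recovery 0 to 10 points, f = 0 or 0.5).

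- 30% acupuncture, 10% sham: from 21.5 × 0.7 − 10 × 0.9 = 6.05 to 11.5 × 0.85 = 9.78. Bias −5.45 to −1.72.
- 10% acupuncture, 30% sham: from 11.5 × 0.9 = 10.35 to 21.5 × 0.9 − 10 × 0.7 = 12.35. Bias −1.15 to +0.85.

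**6. No true effect, dropout 10% acupuncture and 30% sham.** The false difference is g × 0.2 × (1 − f). Rejection rates are simulated for a two-sided 5% t-test against zero, 37 per arm.

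| Recovery in both arms | f | False difference | Rejection rate |
|---|---|---|---|
| 12 | 0 | 2.4 | about 14% |
| 12 | 0.5 | 1.2 | about 8% |
| 8.5 | 0 | 1.7 | about 10% |
| 8.5 | 0.5 | 0.85 | about 6% |

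Reversing the split reverses the sign. With equal dropout the false difference is zero and the rejection rate stays at 5%.

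**The case against.** The other side has several fair points, and most of them limit the size of the concern.

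- **Inputs.** The document gives no sham recovery, no dropout by arm and no timing of dropout. The size of the bias is therefore a range. That both arms improve is plausible so soon after stroke, but it is not a stated figure.
- **Direction.** A reader might infer that LOCF favours acupuncture. The documents do not support that. The direction depends on which arm loses more patients, and with equal dropout and no true effect the mean bias is zero.
- **Power.** A reader might set 0.59 against the 0.88 that 37 fully observed patients per arm would give. With 20% dropout no method keeps 0.88, so part of that gap comes from dropout itself. And 0.59 is the severe end, where no dropout has a week-2 score.
- **Which test.** The power figures above concern the margin test; the false-positive figures concern a two-sided test against zero, which is closest to the t-test in section 2.10. They should not be read together. Against zero, LOCF at f = 0 lowers power only from 99.7% to 96.4%. Against the margin with no true effect, 12 points of recovery and 10%/30% dropout, rejection is under 1%.
- **Open choice.** A reader might infer that the method will be picked once results are known, or that no missing-data sensitivity analysis is planned. The trial design section says that a statistical analysis plan is available with the registration, and it may settle both. Section 2.4 also keeps the statisticians blind to group. Neither inference is safe.

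What does not fall away is that the article itself names LOCF as an acceptable way to fill the primary outcome. Having multiple imputation as the alternative does not remove it.

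**Conclusion.** The concern holds in this limited form: LOCF is stated as an allowed method and should not be available for the primary FMA-UE analysis.

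Under the plan's own effect and 20% dropout, split equally, it costs 1.15 to 2.3 of the 11.5 points, that is 10% to 20%. Margin power then falls from about 0.80 to 0.81 to between 0.76 and 0.59. With unequal dropout the bias may dilute or inflate the difference. With no true effect, a 10%/30% split and 8.5 to 12 points of recovery, the false difference is about 0.9 to 2.4 points and a two-sided test against zero rejects about 6% to 14% of the time. The share of gain at the last visit, the recovery and the split are all assumed.

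Confidence is high that LOCF is unsuitable and lower about the size of the harm. It should be corrected before analysis; it calls for no change to conduct or sample size.

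**What to change.** Delete LOCF from section 2.10 and name one primary method that is valid under missing at random. Either of these would do:

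- multiple imputation, already named in the plan, carried out by arm with baseline and week-2 FMA-UE in the imputation model; or
- an MMRM over week 2, week 4 and 3 months, with baseline FMA-UE as covariate.

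Keep the PPS analysis as supportive. A delta-adjusted analysis, which shifts the imputed scores by stated amounts, would test the missing-at-random assumption and is a useful low-cost addition if the statistical analysis plan does not already hold one.

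The scheduled visits already supply the data. The cost is a change of wording and modest extra programming, with no new data and no more patients.
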